**Secondary aims:**

1. To determine, using sensitive magnetic methods, the effect of each ACT regimen on gametocyte carriage during the six-week trial follow-up period.

2. To determine the duration of post-treatment prophylaxis using passive case detection of symptomatic malaria infections presenting over a period of six months after trial follow-up.

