2. AP (Pyramax) as artesunate 3 mg/kg and pyronaridine tetraphosphate 9 mg/kg once-daily for three days, and
3. AN (Arco) as artemisinin 20 mg/kg and naphthoquine phosphate 8 mg/kg once-daily for three days (as justified above).

Combinations of full, half- or quarter-tablets will be swallowed whole or crushed lightly before administration. AL-treated subjects will be given tablets or suspension with milk; because there is no such recommendation for AP or AN, pharmacokinetic studies our group will perform during 2009 will determine whether these ACTs should also be given with milk. Only the evening AL doses will be unsupervised, being given at home by parents/guardians. Children vomiting within 30 minutes will be re-treated.

Standardized review including microscopy will be scheduled on Days 1, 2, 3, 7, 14, 28 and 42, with all data, including symptoms, unscheduled clinic visits and non-study treatment, entered on detailed case report forms. Children developing uncomplicated or severe malaria will be given DP at the clinic or intramuscular artemether at the local referral hospital, respectively as per the most recent PNG National Treatment Guidelines.23 All blood films will be re-examined by two skilled microscopists blinded to treatment. Slides discrepant for positivity/negativity, speciation or parasitaemia (>3x difference) will be adjudicated by a senior microscopist. The primary endpoints constitute ACPR under WHO-recommended assessment.24 Early treatment failure (ETF) will be taken as the development of severity or an inadequate parasitological response by Day 3. Any child developing parasitaemia between Days 4 and 42 will be considered late parasitological failure (LPF) or, if febrile, late clinical failure (LCF).

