*Background:* We have developed HFGMF gametocyte detection based on the unique metabolism of iron in the parasite and commercially available magnetic separation columns (Miltenyi Biotech). The method relies on magnetic concentration of gametocytes which are then identified more readily on a smear (see Figure 2) than by conventional expert microscopy.29 It has a similar sensitivity to reverse transcriptase PCR (RTPCR, data submitted; see Table), but is much quicker and cheaper.

[figure not shown]

| Gametocyte density | HFGMF (time taken) | Thick film (time taken) | RT-PCR |
| --- | --- | --- | --- |
| 2,970/µL | Positive (<1 minute) | Positive (<1 minute) | Positive |
| 297/µL | Positive (<1 minute) | Positive (7 minutes) | Positive |
| 29.7/µL | Positive (<1 minute) | Positive (28 minutes) | Positive |
| 2.97/µL | Positive (9 minutes) | Negative | Positive |
| 0.297/µL | Negative | Negative | Negative  HFGMF detection at 3/μL |

The method could be used to quantify the gametocidal efficacy of ACT assuming that transmission is unlikely at a gametocyte density <3/μL,30 a threshold detectable by HFGMF but not microscopy.

*Methods:* We will take a small additional sample of mixed capillary blood at each follow-up visit from 25 children in each treatment and species arm on which HFGMF and RTPCR will be performed as well as conventional microscopy. The differences in gametocyte carriage by detection method over time between treatment arms will be determined using General Linear Modelling for repeated measures, applying square-root transformation to allow for the effect of zero values on the density distribution at each time point and identifying important non-treatment-related covariates.

**Sub-study 2: Duration of post-treatment prophylaxis using passive case detection of symptomatic malaria during the six months after trial follow-up** *(Secondary Aim 5)*

*Hypothesis:* The duration of post-treatment prophylaxis for AL, AP and AN is a function of the t½*e* of the non-artemisinin partner drug alone.

*Background:* For some long half-life drugs such as piperaquine, urinary excretion studies suggest unexpected persistence of low plasma concentrations.31 In addition, the antimalarial activity of atovaquone in sera is sustained beyond that predicted by its pharmacokinetic properties.32 Whether these sorts of effects are of clinical importance in ACT-treated patients is unknown, even for DP.

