*Methods:* We will carry out a 6-month period of passive case detection of all trial patients with an ACPR after trial close-out through surveillance of clinic/inpatient records for confirmed malarial episodes at i) Alexishafen/Modilon Hospital and ii) Rabaul Hospital/neighbouring clinics. Our established presence at both sites and our relationship with local health care staff should enable us to overcome potential problems with ascertainment using existing information systems. To examine the effect of treatment on long-term outcome, we will perform a Cox regression analysis of time to first appearance of i) any parasitaemia in-trial or post-trial, and ii) because LPF would not be ascertained during post-trial follow-up, any symptomatic parasitaemia in-trial or post-trial. The mean time to event in each treatment group will be compared with the t½*e* for each scenario.

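### Sub-study 2 sets a per-arm mean time to event against half-life, but with follow-up ending near Day 224 no usable version of that mean is a duration of prophylaxis

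*Protocol*

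**What the plan says.** The hypothesis of Sub-study 2 begins "The duration of post-treatment prophylaxis for AL, AP and AN is a function of the" partner drug's half-life, and holds that nothing else matters. Its Methods give two analyses. The first is a survival model: "To examine the effect of treatment on long-term outcome, we will perform a Cox regression analysis". That model is run for two outcomes. One is defined as "time to first appearance of i) any parasitaemia in-trial or post-trial", and the other counts symptomatic parasitaemia alone. The second analysis is the link to the hypothesis: "The mean time to event in each treatment group will be compared with the" half-life, for each of the two event definitions.

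The observation period is fixed elsewhere. Under Clinical/laboratory procedures, "Standardized review including microscopy will be scheduled on Days 1, 2, 3, 7, 14, 28 and 42". After that, "We will carry out a 6-month period of passive case detection of all trial patients with an ACPR after trial close-out"; Secondary aim 2 describes the same period as "presenting over a period of six months after trial follow-up". The protocol does not say whether the mean is restricted to a horizon, comes from a fitted model, or how children without an episode enter it.

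**The concern.** A mean time to event needs the whole survival curve. Here the curve is seen only to about Day 224, and any child without a recorded episode by then contributes a lower bound and not a time. An analyst following the sentence as written must do one of three things: average over children who had an event, count event-free children at the cut-off, or extrapolate with a model that the protocol does not name. The three give very different figures, and the first two move with the local malaria rate even when the drug's protection is unchanged.

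This sentence is the only stated bridge from the data to the half-life hypothesis. If drugs that differ in protection yield similar means, a reader could wrongly conclude that half-life matters little. If the means are read as durations, values of 100 days or more would be set beside half-lives of 4-6 days (lumefantrine), 7-9 days (pyronaridine) and 2-12 days (naphthoquine), and most of each value would be waiting time for an infection.

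**Working it through.** The protocol gives no sample size, event count or expected mean for this sub-study, so there is no figure of its own to reproduce.

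**Horizon.** 42 days of trial review plus six months (taken as 182 days) gives 42 + 182 = 224 days; 180 to 184 days gives 222 to 226. This takes the six months as starting at each child's Day 42.

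**Model (assumed).** No episodes for L days, then a constant hazard λ per day. L is 14 days on one drug and 42 on the other, a true difference of 28 days. Incidence after protection ends is 0.5, 1 or 2 episodes per child-year. With τ = 224 and S = exp(−λ(τ − L)):

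- share with an event = 1 − S
- unrestricted mean = L + 1/λ
- restricted mean to τ = L + (1 − S)/λ
- events-only mean = L + 1/λ − (τ − L)·S/(1 − S)

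**Worked case, 1 episode per year** (1/λ = 365.25 days).

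- L = 14: S = exp(−210/365.25) = 0.5627. Restricted mean = 14 + 0.4373 × 365.25 = 173.7. Events-only mean = 379.25 − 210 × 0.5627/0.4373 = 109.0.
- L = 42: S = exp(−182/365.25) = 0.6076. Restricted mean = 42 + 0.3924 × 365.25 = 185.3. Events-only mean = 407.25 − 182 × 0.6076/0.3924 = 125.5.

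| Episodes per child-year | Share with event | Events-only means (difference) | Restricted means (difference) | Unrestricted means (difference) |
| --- | --- | --- | --- | --- |
| 0.5 | 22-25% | 114.0 v 129.2 (15.2) | 196.5 v 203.1 (6.6) | 744.5 v 772.5 (28) |
| 1 | 39-44% | 109.0 v 125.5 (16.5) | 173.7 v 185.3 (11.6) | 379.2 v 407.2 (28) |
| 2 | 63-68% | 99.3 v 118.1 (18.8) | 138.8 v 157.2 (18.4) | 196.6 v 224.6 (28) |

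Only the unrestricted mean recovers 28 days. At the two lower rates it lies wholly beyond the observation window.

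**Sensitivity to the share event-free.** With delays of 14 and 28 days (true difference 14), when 5%, 50% or 90% of the shorter-acting arm are event-free at Day 224, the restricted means differ by 13.2, 6.8 and 1.4 days and the events-only means by 12.3, 8.5 and 7.2.

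**Different shape.** With no delay, a hazard ratio of 0.7 and 50% event-free in the reference arm, the unrestricted means differ by 138.5 days, the restricted by 15.9 and the events-only by 3.8.

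**Would a percentile do better?** In the delay model the time by which 20% have had the event is L + 0.223/λ. For L = 14 this is about 177, 95 and 55 days at 0.5, 1 and 2 episodes per year, a swing of about 122 days with protection unchanged. The restricted mean moves by 196.5 − 138.8 = 57.7 days and the events-only mean by 114.0 − 99.3 = 14.7. So a per-arm percentile is the most incidence-dependent of the three. Its between-arm difference, however, is exactly 28 days at every rate in this model. At 0.25 per year the share with an event is 1 − exp(−210 × 0.25/365.25) = 13% for L = 14 and 1 − exp(−182 × 0.25/365.25) = 12% for L = 42, so the 20% level would not be reached.

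**The case against.** **The main analysis is sound.** A reader might infer that the sub-study cannot compare the treatments over the long term, or cannot address Secondary aim 2 at all. The protocol does not support that. Cox regression keeps event-free children as censored, and it is the stated method for the treatment effect. This stands and limits the point to the half-life comparison. A hazard ratio is not a duration, though, so it does not replace that comparison.

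**The estimator may be settled in the analysis plan.** The sentence is compatible with a restricted mean or a model-based mean, and Kaplan-Meier estimation is planned for the trial endpoints. It would therefore be too strong to say the mean cannot be estimated: it can be with a parametric model, and a restricted mean can be without one. What remains is that the protocol itself names the statistic and gives it a meaning that neither the events-only nor the restricted version has.

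**The size is assumed.** Neither the incidence nor the 14- and 42-day delays are in the protocol. Its only rate, suspected cases exceeding 25% of the population per year, is not specific to these children. For vivax any-parasitaemia the loss may be smaller: the cited Day 42 ACPR was 30.3% on AL and 69.4% on DP, so about 70% and 31% respectively had failed before passive surveillance would begin. A claim that the understatement is always large is not supported.

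**Falling transmission.** A reader might infer that the expected decline in transmission biases one arm against another. Allocation is randomised in blocks by site, so concurrent arms should be affected alike. What changes is every per-arm figure and the size of the restricted-mean contrast.

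**Conclusion.** The point holds, confined to the half-life comparison. With observation ending near Day 224 and event-free children censored, the unrestricted mean is not identified without a parametric model, and neither usable per-arm version measures how long a drug protects. Under a 28-day true difference and 0.5 to 2 episodes per child-year, the contrast shrinks to about 15-19 days (events only) or 7-18 days (restricted). These figures rest on the assumed delay-then-constant-hazard model. The loss becomes small if about 5% or fewer are event-free at the cut-off, and is large if half or more are.

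A reader might also infer that a Kaplan-Meier percentile supplies the duration of protection that the mean does not. It does not: per arm it too moves with incidence. Its between-arm difference recovers the full difference in the delay model; without a delay and under proportional hazards that difference would also scale with incidence.

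This should be corrected, but it concerns a secondary aim and leaves the between-arm test intact.

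**What to change.** In the Methods of Sub-study 2, replace the per-arm mean with a between-arm contrast that keeps event-free children as censored, reported with its confidence interval. Either of these would serve:

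- the difference in a Kaplan-Meier percentile that is reached in every arm, with the level fixed beforehand from expected incidence and not set at 20% regardless; or
- the difference in restricted mean time to a stated common day, labelled as restricted.

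Compare these between-arm differences, and not the per-arm values, with the differences in half-life. Add that no per-arm percentile or mean is to be read as the duration of protection, because all of them move with local incidence.

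The cost is a sentence or two, with no new data or visits. The downsides are that a low percentile has a wider interval, and that a restricted-mean difference remains attenuated, so a small one should not be taken as evidence that the drugs protect equally long.

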**ETHICAL ISSUES**

*i) Administration of a non-standard treatment for malaria:*  Two-thirds of the children will receive a non-standard treatment for malaria. However, both AP and AN have been well tested and shown to be fully effective in a variety of other countries and AN is already available in PNG. It is important for future antimalarial treatment policy to have up-to-date data from PNG children on alternative therapies if combinations such as AL start to fail.

*ii) Informed consent and child assent:* The parents/guardians of all participants will give informed verbal and written consent. Children who are able to understand and communicate at an appropriate level will be given a basic outline of the study and will not be recruited if there is clear evidence of non-assent to study procedures.

*iii) Painful and unpleasant procedures (finger pricks, venesection):* These may cause a small amount of pain and bruising. The risk of infection is negligible.

*iv) Volume of blood sampling:* The total volume of blood taken over 6 weeks will be <15mL, representing approximately 2% of a child’s haematocrit. This is not a physiologically significant amount and it should be replaced quickly after successful treatment of malaria.

*v) Arrangements for adverse events during the trial:* Trained health care staff will be at each site during working hours and contactable by mobile phone out of hours if necessary, and a physician will be either on site or also available for telephone consultation if a child develops or presents with any adverse event. If the adverse event is considered severe,

1. the child will be transferred promptly to the nearest major hospital for further management
2. the principal investigators will be informed of the nature of the event within 24 hours
3. the local study physicians and principal investigators will determine whether it is not related, possibly related or definitely related to allocated treatment, or unknown
4. the principal investigators will notify each event to the Data and Safety Monitoring Committee who will consider whether the protocol should be modified as a result of such events. The PNG IMR Institutional Review Board will also be notified promptly of such events using the standard format for such occurrences.

